#### Process evaluation

Observed and independent observations are done for each worker at least once a month. Different activities (delivery of interventions and counselling for consumption of nutrient supplements, coping strategies, personal hygiene, hand washing practices, timely antenatal visits, optimal breast feeding practices and immunization in childhood, etc) conducted by the workers are observed by accompanying them. During these visits, the following aspects are evaluated; the quality of interaction between the workers and the family, whether the questions in the forms are asked correctly, quality of counselling and whether all procedures are performed as planned. During independent visits, the participants are asked whether the worker visited, the activities performed at the visit and the counselling provided.

The study also has a “Program Learning Team” which comprises of two social scientists who conduct interviews and observations around the key study activities. They assess compliance to interventions through interviews and observations. Additionally, in-depth interviews are done with non-responders to anemia and those with inadequate weight gain to ascertain possible reasons. The findings are communicated to the relevant study teams and are used to strengthen intervention delivery through retraining of workers and improvement in processes, whatever is applicable.

#### Outcome ascertainment

Participants in both groups are visited by the independent outcome ascertainment team at the end of pre- and peri-conception period. The symptoms of RTI, depressive symptoms, compliance to interventions, micronutrient, anemia, thyroid and diabetes status are ascertained. During pregnancy, weight gain, compliance to interventions and micronutrient status is assessed. Weight, length, head- and mid-upper arm circumference, child care practices, prevalence of illness and care seeking and hospitalization are assessed during early childhood (Additional file 3).

Weights and lengths are taken by pair of workers using digital weighing scale (model 354; Seca, California, USA) and infantometer (model 417; Seca, California, USA) to the nearest 10 g and 0.1 cm, respectively. Head and mid-upper arm circumference is taken using a measuring tape (model 212; Seca, California, USA) [66–68].

#### Laboratory investigations

At enrolment, ~ 10 ml blood sample is obtained from women in the intervention group to screen for anemia, thyroid disorders, diabetes, RPR and micronutrient assays. Around 10 ml blood is taken from women in both intervention and control groups when they report pregnancy or do not get pregnant during 18 months of the pre- and peri-conception period, in the third trimester of pregnancy and at 6 months postpartum from women in the intervention and control groups for anemia assessment, micronutrient status and inflammatory markers. 5 ml blood will be collected from children at 24 months of age in both groups for micronutrient assays.

The samples are centrifuged and serum is stored in a − 80 °C deep freezer in the “Clinical and Research Laboratory” set up in the field office, which is accessible only to the laboratory managers. Laboratory investigations are done in an accredited commercial laboratory (Strand-Quest Diagnostics Laboratory) and at referral hospitals (Safdarjung Hospital). The body composition analysis will be done by isotope dilution technique using deuterium oxide (2H2O) at 1 month of age in a subsample [69]. The infant saliva samples will be analyzed for enrichment of deuterium by Fourier transform infrared (FTIR) spectrophotometry [69].

#### Ultrasounds for assessment of pre term birth and fetal growth restriction

Ultrasounds in enrolled women during pregnancy (intervention and control groups) are done at the designated ultrasound centers. A trans-abdominal ultrasound is scheduled between 9 and 13 weeks of gestation to estimate gestational age calculated by fetal crown-rump length (CRL). If CRL is > 95 mm, femur length and head circumference will be used to assess gestational age [70]. Repeat ultrasounds are done at 26–28 weeks and 35–36 weeks of gestation and biparietal diameter (BPD), occipito-frontal diameter (OFD), head circumference (HC, using ellipse facility), abdominal circumference (AC using ellipse facility) and femur length (FL) are measured. All measurements are taken by trained radiologists according to the INTERGROWTH-21 standards [71].

Three measurements are taken for each fetal biometric variable: CRL, BPD, OFD, FL, HC and AC, with the woman in the lateral recumbent position [71]. The radiologists performing the scan are blinded to the group allocation of the pregnant women. All digital images are stored in a secured server. Images from 10% of all study participants are randomly selected and sent for external review for quality assurance.

#### Training and standardization

Prior to study initiation, all staff were trained in the study objectives, study strategy and in good clinical practices [72]. Additionally, each team underwent intensive training in their area of work (door-to-door survey, consenting, anthropometry measurements, assessment of morbidity, nutritional and psychosocial counselling, etc).

Inter- and intra-observer standardization exercises for weight, length, height, mid upper arm circumference and head circumference were conducted before study initiation for the SET, the independent outcome ascertainment team and for all other workers who take weight and length measurements; these are repeated 6 monthly. Weighing scales and infantometers are calibrated daily using standard weights and length measurement rods.

#### Study oversight and monitoring

Coordinators designated for each activity oversee the work of their teams. Weekly status reports are shared with the investigators. Periodic reviews meetings are organized between the study teams, coordinators and the investigators.

The WHO, Geneva and Biotechnology Industry Research Assistance Council (BIRAC), Department of Biotechnology, Government of India are responsible for oversight of the study. Technical staff from WHO and Bill & Melinda Gates Foundation interact with the investigators through conference calls once in two months and twice-yearly site visits to review study progress.

#### Data management

Data are captured electronically on tablets and mobile phones. Range and logical checks are built in to ensure data quality. The data management centre is set up in the field office. Real time data are transferred to the server. Logical errors and checks across different forms are run twice weekly; queries generated are given to study team for resolution and corrections incorporated.

#### Data and safety monitoring committee

A Data Safety Monitoring Committee (DSMC) has been constituted by the WHO and BIRAC to review the data, monitor the progress of the trial and assess safety of the interventions. The committee reviews data twice a year. The members include - an epidemiologist, a statistician and a clinician and a social scientist. An interim analysis will be conducted in a blinded manner when 50% of the babies in the study are born, a second review will be done when 50% of the babies in the study reach 2 years of age. The committee will advise the team on study continuation, modification or termination based on pre-decided stopping rules. This is a low-risk trial and serious adverse events are not anticipated. However, all deaths in enrolled participants are being reported to the local ethics committee and the World Health Organization for further communication to the DSMC. Additionally, adverse events reported with any supplement are being documented and all severe adverse events will be reported to the ethics committees and the DSMC.

### Statistical analyses

#### Primary comparisons

The primary analysis will be factorial, for comparison of the pre- and peri-conception intervention package (pre- and peri-conception intervention package alone or with enhanced antenatal, postnatal and early childhood care package i.e. Group A + B) with no pre- and peri-conception intervention package (enhanced antenatal, postnatal and early childhood care package alone or routine care i.e. Group C + D), and the enhanced antenatal, postnatal and early childhood care (with pre- and peri-conception intervention package or enhanced antenatal, postnatal and early childhood care alone i.e. Group A + C) with no enhanced antenatal, postnatal and early childhood care (pre- and peri-conception intervention package alone or routine care i.e. Group B + D) on birth outcomes (mean birth weight and length, proportion stunted at birth, proportion of babies born preterm and spontaneous preterm births, SGA and LBW) and mean length for age z-score and proportion stunted at 24 months.

In addition to the factorial analysis, we will also examine the impact of the combined pre- and peri-conception intervention package and enhanced antenatal, postnatal and early childhood care (Group A) on birth outcomes and attained length at 24 months of age, compared to routine care (Group D).

We will examine if there is an interaction between the intervention package delivered during peri-preconception period and that delivered during antenatal and early childhood period on primary outcomes.

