We are conducting an individually-randomized controlled trial in urban and peri-urban low- to mid-socioeconomic neighborhoods in Delhi, India to ascertain the impact that can be achieved on birth outcomes, growth and development in children by intervening before women become pregnant, in addition to delivering interventions during pregnancy and postnatal life. The study aims to achieve optimal growth and development in infants and children through concurrent delivery of an integrated package of evidence-based interventions covering the continuum from the pre- and peri-conception period to early childhood. We used a factorial design so that the impact of intervening during the pre-pregnancy period alone could also be assessed.

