### Objectives

The primary objective is to determine the effect of integrated and concurrent delivery of interventions to improve health, nutrition, WASH and psychosocial status during the pre- and peri-conception period alone (pre- and peri-conception intervention package); during pregnancy and early childhood (enhanced antenatal, postnatal and early childhood care) and; throughout the pre- and peri-conception period, pregnancy and early childhood (pre- and peri-conception intervention package and enhanced antenatal, postnatal and early childhood care), on preterm birth, LBW and SGA, and stunting at 24 months of age compared to routine care and additionally, to assess whether the effect of these interventions differs by maternal stature (< 150 cm or ≥ 150 cm).

The secondary objectives are to determine the effect of the same package on nutritional status, morbidity and neurodevelopment in children, and on women’s nutritional status and morbidity in the pre- and peri-conception, pregnancy and postpartum periods.

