We propose to enrol a total of 13,500 eligible women (6750 in pre- and peri-conception intervention package group and 6750 in control group) based on the following assumptions: 45% of reproductive-age women randomized get pregnant in the 18 months of the pre- and peri-conception intervention period, 30% loss (abortions, still births, maternal deaths, moving away, refusals) between pregnancy and live birth and 20% loss (loss-to-follow-up and child deaths) between birth and 24 months of age.

We will get ~ 1100 live births per group. This will enable us to detect a 25% difference in preterm births, proportion LBW and SGA between pre- and peri-conception package alone and control group (A + B vs C + D) and enhanced antenatal, postnatal and early childhood care alone and control group (A + C vs B + D) and a mean difference of 0.15 SD in LAZ score at 24 months for the above comparisons.

We will get at least 600 children in each of the four groups (A, B, C, D) at 24 months. We will be able to detect 0.2 SD difference in mean LAZ score at 24 months and 0.2 SD difference in birth weight and birth length between pre- and peri-conception intervention package and enhanced antenatal, postnatal and early childhood care and control group.

The sample size of ~ 2400 (at least 600 children in each of the 4 groups) at 24 months of age will also allow us to detect an interaction odds ratio (lOR) of ≥1.70 to 1.85 in the proportion of stunted children among short mothers (< 150 cm) and among tall mothers (≥ 150 cm) between the control (routine care) and the intervention group who received the intervention package throughout, with 80% power and 95% confidence level.

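### The primary objective sets each package against routine care, but only the combined regimen has its own planned contrast, and the sample size section labels the factorial margins as effects of each package alone

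*Protocol article*

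**What the plan says.** Write A for both packages, B for the pre- and peri-conception package only, C for the pregnancy and early childhood package only, and D for routine care.

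- **Protocol article, Objectives.** Three regimens are listed: "during the pre- and peri-conception period alone (pre- and peri-conception intervention package"), then "during pregnancy and early childhood (enhanced antenatal, postnatal and early childhood care"), then both throughout. They are assessed on the birth outcomes "and stunting at 24 months of age compared to routine care". In group terms these are B vs D, C vs D and A vs D.
- **Background.** The stated reason for the design is: "We used a factorial design so that the impact of intervening during the pre-pregnancy period alone could also be assessed".
- **Primary comparisons.** The first margin sets "pre- and peri-conception intervention package alone or with enhanced antenatal, postnatal and early childhood care package i.e. Group A + B" against "enhanced antenatal, postnatal and early childhood care package alone or routine care i.e. Group C + D". The second, A+C vs B+D, is built the same way. The only further contrast is A vs D, introduced by "In addition to the factorial analysis, we will also examine the impact of the combined pre- and peri-conception intervention package". The interaction between the two packages will also be examined.
- **Sample size.** The title of Table 1 attaches the word alone to both margins. The text below the tables describes a detectable difference in preterm birth, "proportion LBW and SGA between pre- and peri-conception package alone and control group (A + B vs C + D"), and treats A+C vs B+D likewise.

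**The concern.** Two of the three comparisons in the primary objective have no planned contrast of their own, and the Sample size section names a different quantity as if it were the missing one. In A+B vs C+D, half of the treated women also receive enhanced pregnancy and childhood care, and half of the so-called control women receive that care rather than routine care. The contrast averages the pre-conception effect over women with and without the other package. Primary comparisons describes it correctly; the Sample size labels do not.

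At stake is which number is reported as the answer to the pre-pregnancy question, the one Background gives as the reason for the factorial design. If the packages overlap, the margin understates the effect against routine care; if they reinforce each other, it overstates it. The Conclusion expects the pre-conception findings to inform policy on such programmes. For a setting with routine antenatal care only, the directly relevant estimate is, in my judgement, B vs D. Whether the margins are legitimate as primary tests is not in question.

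**Working it through.** **Inputs (Sample size, Tables 1 and 2 and text).** Single package: 0.15 SD or 25% relative reduction. Combined: 0.20 SD or 30%. Control rates: LBW 25%, preterm 12%. Group sizes: about 1,100 live births and at least 600 children at 24 months. The plan's own rates give 13,500 × 0.45 × 0.70 / 4 = 1,063 live births and 1,063 × 0.80 = 850 children per group. I assume equal groups.

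**The plan's figures first.** For mean LAZ at 90% power and two-sided 5%, n = 2(1.960 + 1.282)² / d². With d = 0.15 this gives 934 (stated 935); with d = 0.20, 526 (stated 527). For LBW, the two-proportion formula without continuity correction gives 918 and 624, as stated. So Table 1 sizes the margins at 0.15 SD or 25%, and Table 2 sizes A vs D at 0.20 SD or 30%.

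**Margin against alone effect, mean scale.**
- Margin = [(A − C) + (B − D)] / 2; alone effect = B − D. They are equal only if A − C = B − D, that is, without interaction.
- Set D = 0, B = C = 0.15, A = 0.20. Margin = [(0.20 − 0.15) + 0.15] / 2 = 0.10 SD, against 0.15 SD alone. The implied interaction is 0.20 − 0.30 = −0.10 SD.
- Hold the single effects at 0.15 SD and vary the combined effect:

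| Combined effect (SD) | Margin (SD) | Alone (SD) |
|---|---|---|
| 0.20 | 0.10 | 0.15 |
| 0.25 | 0.125 | 0.15 |
| 0.30 | 0.15 | 0.15 |
| 0.35 | 0.175 | 0.15 |

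**Risk-ratio scale.** With B = C = 0.75 and A = 0.70 times the risk in D, the marginal RR is (0.70 + 0.75) / (0.75 + 1.00) = 0.83, against 0.75 alone. The two coincide if A is 0.75 × 0.75 = 0.5625 times the risk in D: (0.5625 + 0.75) / 1.75 = 0.75.

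**Consistency of the two tables.** The two margins always sum to A − D. Two margins of 0.15 SD therefore imply A − D = 0.30 SD, and A − D = 0.20 SD implies margins averaging 0.10 SD.

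**What the simple contrasts would deliver.**
- LAZ, 95% half-width 1.96√(2/n): at 600 per group 0.113 SD (margin, 1,200 per side: 0.080); at 850 per group 0.095 SD (margin, 1,700 per side: 0.067). The ratio is √2, about 1.4.
- RR 0.75 at 1,063 per group, with variance of log RR = (1 − p₁)/(np₁) + (1 − p₀)/(np₀): 95% CI 0.64 to 0.88 for LBW and 0.58 to 0.96 for preterm birth.
- Power of B vs D at the tabulated single-package effects: about 74% for LAZ at 600 per group, 63% for preterm birth and 94% for LBW at 1,100 per group.
- Power to detect an interaction of −0.10 SD in LAZ at 600 per group: the standard error is √(4/600) = 0.082, so power is about 23%.

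**The case against.** The strongest reply is that the governing section is right. Primary comparisons spells out that each margin mixes women with and without the other package, and the Sample size text prints the group letters beside each loose label. Marginal analysis is standard for a 2×2 factorial and is where the power lies. All of this stands, and it limits the fault in the text to labels and to two unnamed contrasts.

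Several further points also stand.

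- **The plan does not commit to non-additive packages.** A reader might infer from Tables 1 and 2 that it does. But the combined effect is described as at least twice that of a single intervention, which is a floor, and Table 1 attaches 0.15 SD to the margin itself. The tabulated values can be read as detectable effects, not forecasts.
- **The synergy language does not settle it.** The Abstract and Background raise synergy between domains (health, nutrition, WASH, psychosocial care) delivered together. The two factors are time periods, so that text says nothing about how the two packages combine.
- **The objective says alone only once.** The word is attached to the pre-conception package. C vs D follows from the three-item list with a routine-care comparator, and from the title of Table 1, which uses the word for both.
- **Part is covered.** Main effects promises outcomes for the different groups, and an interaction examination is planned, so the simple effects can be estimated. What follows from an interaction may be set out in an analysis plan that is not shown, and its absence here is no fault.

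What the reply does not remove is that the stated objective and the listed contrasts differ, and that the Sample size labels hide the difference. Nor could a non-significant interaction close the gap: with about 23% power at −0.10 SD, it would not justify reading a margin as an alone effect.

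**Conclusion.** The point holds as a mismatch of objective, contrast and label. Of the three comparisons with routine care, only A vs D is planned as such, and the margins are described in the Sample size section as something they are not unless the packages do not interact on the analysis scale.

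The size depends on a reading the document allows but does not require. With 0.15 SD or 25% for one package and 0.20 SD or 30% for both, all against routine care, a margin reported as the alone effect would be one third too small in SD terms (0.10 against 0.15), or RR 0.83 in place of 0.75. The gap is 0.025 SD at a combined effect of 0.25 SD and nil at 0.30 SD. It would be wrong to say that the plan understates the alone effect by one third without that condition, or that the factorial primary analysis is invalid. The documents support neither. Equal group sizes are assumed throughout.

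**What to change.** 1. Keep A+B vs C+D and A+C vs B+D as the primary factorial analysis.
2. Prespecify B vs D and C vs D as supporting estimates for the two objectives set against routine care, reported beside A vs D with 95% confidence intervals. Take them from the GLMs already named under Main effects, with both factors and their product; the planned interaction examination needs that model anyway.
3. In the title of Table 1 and in the Sample size text, describe each margin as the average effect of one package across the levels of the other, and drop the labels alone and control group for these contrasts.

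The cost is some rewording and two more contrasts per primary outcome. The intervals are about 1.4 times as wide as for the margins, and power is modest for some outcomes (about 74% for LAZ at 600 per group, 63% for preterm birth at 1,100). The additional contrasts also add to the number of comparisons. For both reasons, present them as estimates with intervals and not as powered tests.

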#### Definitions of primary outcomes

Birth weight will be defined as weight taken by the study team at day 7 after birth and birth length as length taken by the study team any time within the first 7 days after birth to ensure comparability across the groups. Weight taken on day 0 is available for large proportion of infants. However, this proportion is likely to be unequal between the intervention groups (A + C) compared to control groups (B + D) because of greater ability to contact the intervention group mothers immediately after birth. We will therefore use weight on day7 taken consistently on the same day for both the groups as a measure of birth weight.

LBW will be defined as weight < 2500 g on day 7 after birth; proportion stunted as length-for-age z-score < − 2SD according to WHO standards [58]. Gestation at birth will be estimated by subtracting date of birth from date of dating ultrasound and adding it to gestational age as assessed by dating ultrasound according to INTERGROWTH-21 [70]. Preterm births will be defined as births occurring at < 37 completed weeks of gestation. Spontaneous preterm births will be defined as births occurring at < 37 weeks of gestation and preterm pre-labor rupture of membranes or spontaneous onset of labor.

Birth weight centiles will be calculated using the INTERGROWTH-21 standard based on day-7 weight and gestational age at birth [70]. SGA will be defined as birth weight centile <10th and < 3rd as per INTERGROWTH-21 standard [70]. Length-for-age z-score will be calculated based on length measured at 24 months (±28 days) and proportion stunted will be defined as those with length-for-age z-score < − 2 SD by WHO standards [58].

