### Sample size

Sample sizes were calculated for 90% power and 95% confidence level except for the preterm birth outcome for which the power is 80% for comparison between effect of pre- and peri-conception intervention package and enhanced antenatal, postnatal and early childhood care. Larger effect sizes than those shown for single interventions were assumed for the combined effect of pre- and peri-conception intervention package, enhanced antenatal, postnatal and early childhood care group [14–16]. A 1.5 times higher effect size for the impact of either pre- and peri-conception intervention package or enhanced antenatal, postnatal and early childhood care compared with control, and at least 2 times higher for combined effect of pre- and peri-conception intervention package and enhanced antenatal, postnatal and early childhood care compared to control was assumed (Tables 1 and 2).

**Table 1 Tab1:** Sample size estimates for effect of pre- and peri-conception intervention package alone A + B vs C + D) or Enhanced antenatal, postnatal and early childhood care alone (A + C vs B + D)

	Main effect size	Sample size per two groups
Linear growth at 24 months		
- Mean length-for-age z-score (LAZ)	0.15 SD (absolute value 0.65 cm at 24 mo)	935
- Proportion stunted (30%)	25% relative reduction	772
Birth weight/birth length	0.15 SD (absolute value 75 g birth weight and 0.35 cm birth length)	935
Proportion LBW (25%)	25% relative reduction	918
Preterm birth (12%) [35]	25% relative reduction	2193
SGA at birth (36%) [10]	25% relative reduction	558

90% power and 95% confidence level for all outcomes

**Table 2 Tab2:** Sample size estimates for the combined effect of pre- and peri-conception intervention package and enhanced antenatal, postnatal and early childhood care (A vs D)

	Main effect size	Sample size per group
Linear growth at 24 months		
- Mean LAZ	0.20 SD (absolute value 0.80 cm at 24 mo)	527
- Proportion stunted (30%)	30% relative reduction	491
Birth weight/birth length	0.20 SD (absolute value 100 g birth weight and 0.45 cm birth length)	527
Proportion LBW (25%)	30% relative reduction	624
Preterm birth (12%) [35]	30% relative reduction	1100
SGA at birth (36%) [10]	30% relative reduction	381

90% power for all outcomes except 80% for preterm births. 95% confidence level for all outcomes

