### Outcome measures

The primary outcomes include proportion preterm birth (ultrasound-confirmed gestational age at birth < 37 completed weeks); proportion SGA (birth weight centile <10th as per INTERGROWTH-21 standard) on day 7 of birth; proportion LBW (birth weight < 2500 g); mean birth weight and length; attained length (LAZ) at 24 months of age and proportion stunted (LAZ < -2 SD).

The list of secondary outcomes along with the timing of measurements during the pre- and peri-conception, pregnancy and postnatal periods are provided in Additional file 3.

The key secondary outcomes for children are proportion stunted at 6 and 12 months, wasted and underweight at 6, 12 and 24 months, weight and length trajectories from birth to 24 months, body composition (in a subsample) at 1 month of age and neurodevelopment at 6, 12, 18 and 24 months (in a subsample), micronutrients and anemia status at 24 months, morbidity and hospitalization from birth to 24 months (Additional file 3).

The key secondary outcomes for women are micronutrients and anemia status, depressive symptoms and infection at the end of pre- and peri-conception, during pregnancy and postpartum period (Additional file 3).

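### Birth length may be taken on any of days 0–7 although the plan expects earlier contact in the enhanced-care groups, so mean birth length may be biased against the antenatal package

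*Protocol article*

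**What the plan says.** All references are to the protocol article.

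- **Definitions of primary outcomes, weight.** Day-0 weights exist for many infants, but "this proportion is likely to be unequal between the intervention groups (A + C) compared to control groups (B + D"), and the reason given is "because of greater ability to contact the intervention group mothers immediately after birth". The conclusion drawn is: "We will therefore use weight on day7 taken consistently on the same day for both the groups as a measure of birth weight".
- **Definitions of primary outcomes, length.** The same paragraph defines "birth length as length taken by the study team any time within the first 7 days after birth to ensure comparability across the groups". It names no target day and gives no rule for choosing among several lengths.
- **Outcome measures.** The primary outcomes include "mean birth weight and length". Primary comparisons lists both again, for A + B vs C + D and A + C vs B + D, and adds A vs D on birth outcomes.
- **Sample size, Table 1.** The factorial comparisons are planned on "0.15 SD (absolute value 75 g birth weight and 0.35 cm birth length"), with "90% power and 95% confidence level for all outcomes". Table 2 plans A vs D on "0.20 SD (absolute value 100 g birth weight and 0.45 cm birth length").
- **Main effects.** Continuous outcomes are compared as a difference in means from a Gaussian model with identity link.
- **Comparability between the two groups.** Adjustment is foreseen for imbalanced characteristics, in the context of the baseline table.

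**The concern.** The plan identifies a bias, cures it for weight, and leaves it open for length in the same paragraph. If early contact is more frequent in A + C, a window of days 0–7 lets age at measurement follow allocation. Newborns lengthen over that week, so the group measured earlier looks shorter for a reason unrelated to the intervention.

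The error would be systematic, so the large sample does not dilute it; it only makes a shifted estimate more precise. It would understate the benefit of the enhanced antenatal package on a primary outcome and, if there were no true effect, could produce an apparent harm. The stated analysis does not remove it: the model is a plain difference in means, and the adjustment rule concerns baseline characteristics, whereas age at measurement arises after randomisation.

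**Working it through.** **1. The plan's own figure.** For two means, n per side = 2 × (1.960 + 1.282)² / d².

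- d = 0.15: 2 × 10.507 / 0.0225 = 934 (Table 1: 935).
- d = 0.20: 2 × 10.507 / 0.04 = 526 (Table 2: 527).

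Both are reproduced. The implied SD of birth length for the factorial comparison is 0.35 / 0.15 = 2.33 cm.

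**2. Expected numbers.** From the Sample size section: 13,500 × 0.45 × 0.70 = 4252 live births, or 2126 per pooled pair. Without timing bias, power for 0.35 cm is 90.0% at 935 per pair and 99.8% at 2126 per pair.

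**3. Bias.** Bias = growth per day × gap in mean age at measurement. The document gives neither quantity. Both are assumptions here: 0.05, 0.10 or 0.15 cm per day, and a gap of 1, 2 or 3 days.

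| Growth (cm/day) | 1 day | 2 days | 3 days |
|---|---|---|---|
| 0.05 | 0.05 cm (14%) | 0.10 cm (29%) | 0.15 cm (43%) |
| 0.10 | 0.10 cm (29%) | 0.20 cm (57%) | 0.30 cm (86%) |
| 0.15 | 0.15 cm (43%) | 0.30 cm (86%) | 0.45 cm (129%) |

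Percentages are of 0.35 cm. For A vs D, planned on 0.45 cm, the same range is 0.05 / 0.45 = 11% to 0.45 / 0.45 = 100%.

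**4. Consequence for A + C vs B + D.** Standard error = 2.33 × √(2/n), two-sided 5%, normal approximation. Power is computed at a true effect of 0.35 cm minus the bias. The last column is the chance of a significant result against the package when there is no true effect (nominal 2.5%).

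| Bias (cm) | Power, 935 per pair | Power, 2126 per pair | Significant against the package under no effect, 2126 per pair |
|---|---|---|---|
| 0.05 | 79% | 98.7% | 10% |
| 0.10 | 64% | 94% | 29% |
| 0.20 | 28% | 55% | 80% |
| 0.30 | 7% | 10% | 99% |
| 0.45 | 0.2% | 0% | 100% |

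**5. What a given gap requires.** Suppose the groups differ only in the share measured on day 0, and everyone else is measured on day 7. The gap is then 7 days × the difference in shares.

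- A difference of 10 percentage points gives 0.7 day, hence 0.035–0.105 cm (10–30% of 0.35 cm) at 0.05–0.15 cm per day.
- A 1-day gap needs 1/7 = 14 points; a 3-day gap needs 3/7 = 43 points.
- Cancelling the full 0.35 cm needs a gap of 7.0, 3.5 or 2.3 days at 0.05, 0.10 or 0.15 cm per day, that is 100, 50 or 33 points.

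**6. Comparisons affected.** The contact difference is between A + C and B + D, so it enters that comparison and A vs D. In A + B vs C + D each side contains one enhanced-care group, so the timing difference largely cancels.

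**The case against.** The strongest reply is that the article does not say when length is taken in either group. Its remark about unequal contact concerns day-0 weight and says only that inequality is likely. Outcome data come from an independent ascertainment team that visits both groups. The home visit soon after discharge, described under intervention delivery, is made by a different team and does not show that outcome lengths are taken earlier in A + C. Visit timing may be set out in Additional file 3 or the schedule figure, which are not visible here. This stands as far as certainty goes: a reader might infer that A + C infants will be measured younger, but the document supports only that they may be.

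A reader might also infer that the artefact would hide the whole planned effect. The document does not support that: it gives neither growth per day nor an age gap, and full cancellation needs a large difference in early measurement (step 5). At the expected number of births, the mild cases leave power above 90%, although the estimate remains biased.

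Third, a reader might extend the error to stunting at birth. That outcome is defined by a length-for-age z-score, which is already indexed to age; how exactly age enters is a computing detail that an article may leave to the analysis plan.

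Finally, an article may leave covariates to the analysis plan. That is fair for the missing age term alone. It does not answer the main point, which is that a stated rule conflicts with the reason stated for it.

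**Conclusion.** The point holds in limited form. The length definition claims comparability on grounds that the next sentences of the same section undercut, and nothing visible corrects for it. Following the rule as written can bias mean birth length against the enhanced antenatal package in A + C vs B + D and A vs D.

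Under the two stated assumptions the bias is 0.05–0.45 cm, or 14–129% of the planned 0.35 cm. It may well be at the small end, and the true timing by group is unknown. Even at 0.05 cm the chance of a falsely significant adverse result would be about 10% instead of 2.5%. Birth weight, LBW, SGA, preterm birth and the 24-month outcomes do not depend on this window. The bias cannot create a false benefit on birth length.

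**What to change.** - Analyse birth length with exact age in days at measurement in the model, or as a z-score at exact age.
- Where an infant has several lengths, choose by one pre-set rule with the same target day in all four groups: day 7 where a day-7 length exists.
- Tabulate age at length measurement by group.
- Confirm that the z-score for stunting at birth uses exact age in days. This is a confirmation, not a separate correction.

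The cost is slightly more analysis work and a few sentences in the outcome definition, settled before birth lengths are compared by group. The planned sample size stands. Restricting the analysis to day-7 lengths is not required: the article confirms a day-7 weight but not a routine day-7 length, and recruitment began in July 2017, so such a restriction could discard lengths already collected. Age adjustment relies on timing within the week being otherwise unrelated to infant size, which is a further reason to report the timing by group.
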